# Enhancing Adherence to Continuous Positive Airway Pressure Therapy in Patients With Obstructive Sleep Apnea Using Augmented Reality: Protocol for a Randomized Controlled Trial

**DOI:** 10.2196/69757

**Published:** 2025-05-06

**Keywords:** obstructive sleep apnea, continuous positive airway pressure, augmented reality, adherence, feasibility

## Abstract

**Background:**

Continuous positive airway pressure (CPAP) therapy is the gold standard treatment for treating obstructive sleep apnea (OSA). However, patient adherence to CPAP therapy remains a critical challenge, with many individuals finding it difficult to maintain consistent use due to discomfort, lack of understanding, or perceived inconvenience. Augmented reality (AR) offers a novel approach to overcoming these barriers by providing interactive real-time guidance to users, potentially enhancing adherence rates.

**Objective:**

This clinical trial aims to examine the feasibility of AR implementation and the effect of AR on improving CPAP adherence in patients with OSA.

**Methods:**

A randomized controlled trial with a parallel assignment will be conducted. Participants will be randomly assigned to either an experimental group receiving AR-guided CPAP therapy or a control group receiving standard care. The study will span 6 months, with assessments at baseline (T0), and with follow-ups at 1 month (T1), 3 months (T2), and 6 months (T3) post intervention. The primary outcome measure is CPAP adherence, defined as using the CPAP device for more than 70% of sleep time, with a minimum of 4 hours per night. Secondary outcomes will evaluate the common adverse effects associated with CPAP therapy, device usability, and time required for CPAP machine use education.

**Results:**

This study is funded by the Ministry of Science and Technology, Taiwan (August 2023 to July 2026) and was registered in August 2024 (ClinicalTrials.gov NCT06520592). Participant recruitment is scheduled to begin in April 2025, and by September 2025, we expect to have enrolled 40 participants (50% of the target sample of 80). Preliminary analyses of CPAP adherence at 1 month and usability data are currently underway. Final data collection is anticipated to be completed by December 2025, with results expected to be published by Fall 2026.

**Conclusions:**

Anticipated findings suggest that AR-guided CPAP therapy may significantly enhance patient adherence by improving mask fitting and providing effective, interactive education. If validated, this innovative approach could pave the way for more personalized technology-driven interventions in OSA management and other chronic conditions requiring long-term therapy adherence.

**Trial Registration:**

ClinicalTrials.gov NCT06520592; https://clinicaltrials.gov/study/NCT06520592

**International Registered Report Identifier (IRRID):**

PRR1-10.2196/69757

## Introduction

Obstructive sleep apnea (OSA) is a prevalent sleep disorder characterized by repetitive episodes of upper airway obstruction during sleep, which results in low oxygen saturation or frequent awakenings [1]. It has been associated with significant health risks, including cardiovascular diseases [2], cognitive impairment [3], and decreased quality of life [4]. Continuous positive airway pressure (CPAP) therapy is a strongly recommended treatment for OSA according to the clinical practice guidelines of the American Academy of Sleep Medicine. It effectively mitigates the associated risks by maintaining airway patency during sleep [5]. However, adherence to CPAP therapy remains a significant challenge, as many patients struggle to use the device consistently due to physical discomfort [6] and lack of proper guidance or without follow-up care [7].

Guiding patients in disease-related knowledge through educational materials to change their adherence to medical treatment is a commonly used method in clinical practice [8]. However, the effectiveness of guiding middle-aged and older individuals through printed educational materials is often limited. Kim and Oh [9] conducted qualitative interviews with 16 frontline nurses in South Korea and attempted to examine the situation of older adults in receiving health education and health literacy through their perspective. The study found that older adults struggle to understand educational content due to declines in physical and cognitive functions.

The Information-Motivation-Behavioral Skills model suggests that patients’ adherence behavior is driven by their level of information, motivation, and behavioral skills [10]. Augmented reality (AR) applications have the potential to significantly enhance patient adherence to therapeutic regimens through engagement and understanding [9,11]. AR applications can provide personalized real-time information in an engaging format. A systematic review and meta-analysis, which included 11 articles, found that AR can be a tool in physiotherapy to improve older adults’ balance, especially in patients with Parkinson disease [11]. In addition, AR can enhance motivation through interactive features, such as progress tracking and gamification, which make the therapy experience more rewarding [12]. Ideally, by guiding patients in the correct use of their devices, AR can also enhance the behavioral skills necessary for successful adherence.

Previous studies have explored various interventions to improve CPAP adherence, including standardized care procedures [13], cognitive behavioral therapy [14], troubleshooting [15], and telemonitoring [16]. However, the integration of AR technology into CPAP management is a novel approach. Limited research has been conducted on the application of AR in this context, making this study one of the first to investigate its potential impact on OSA management. By addressing the gap in the literature, this study aims to contribute to the growing body of knowledge on innovative strategies to enhance adherence to CPAP therapy.

This study hypothesizes that AR-guided CPAP therapy can enhance patient engagement and understanding of CPAP therapy among patients with OSA, and patients receiving AR-guided CPAP therapy will show higher adherence rates compared to those receiving standard care.

## Methods

### Study Design

This parallel group randomized controlled trial is designed to evaluate the effectiveness of AR-guided CPAP therapy on patient adherence among individuals diagnosed with OSA. Participants will be randomly assigned to either the experimental group (AR-guided therapy) or the control group (standard care) by the blocking sample method. Aside from the AR component, both groups will receive identical standard care. An assistant researcher ([name]) generated the random allocation sequence, case managers enrolled participants with OSA, and an assistant researcher ([name]) assigned participants to interventions. In this study, we will blind assessors and investigators. The study will follow participants over 6 months, with data collection points at baseline (T0), and follow-ups at 1 month (T1), 3 months (T2), and 6 months (T3) post intervention.

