#### Exclusion Criteria

We will exclude those with previous use of positive pressure ventilators, a diagnosis of central sleep apnea, a presence of uncontrolled acute mental illness, or a terminal illness.

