#### Standard Care Group

Participants assigned to the standard care group will have their mask size visually checked by a case manager, who will also teach them how to use the CPAP machine.

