### Procedure

Participants diagnosed with moderate to severe OSA through polysomnography will be assessed for their willingness to participate in the study by the principal investigator. Patients who agree to undergo CPAP therapy and sign the institutional review board permit will be referred to the clinical trial. A research assistant will then contact potential participants via telephone to reconfirm their willingness to enroll. Upon confirmation, the research assistant will assist in scheduling the clinical trial and coordinating regular follow-ups at T1, T2, and T3 to assess CPAP adherence and evaluate treatment-related adverse effects (Figure 2).

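### Case managers are named as enrollers under blocked allocation and also deliver control-arm care, so they might predict some allocations; entry should be separated from care and the two accounts of it reconciled

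*Protocol article*

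**What the plan says.** All places are in the protocol article, under Methods.

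- **Study Design.** Participants are allocated to AR-guided therapy or standard care "by the blocking sample method". One assistant researcher "generated the random allocation sequence", an assistant researcher "assigned participants to interventions", and "case managers enrolled participants with OSA". Blinding is declared for assessors and investigators; case managers are not mentioned. The arms are meant to differ only by the AR component.
- **Sample Size.** 80 participants, 40 in each group.
- **Standard Care Group.** Control participants "will have their mask size visually checked by a case manager, who will also teach them how to use the CPAP machine".
- **Accuracy of Estimated Nasal Size.** The AR system's recommended size is compared with the case manager's estimate at T0.
- **Exclusion Criteria.** Most entry criteria are matters of record, but the exclusions include "a presence of uncontrolled acute mental illness" and terminal illness, which need judgement.
- **Procedure.** The principal investigator assesses willingness and the patient signs consent. Then: "A research assistant will then contact potential participants via telephone to reconfirm their willingness to enroll". The same assistant schedules the trial visits. Case managers do not appear in this account.

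**The concern.** Study Design gives enrolment to the staff group that, according to Standard Care Group, carries out control-arm care. Whoever delivers that care knows those patients' arm. Someone who also enrolled every patient would know that the others were allocated to AR. In a balanced block, knowing the past allocations tells you something about the next one, even if the list itself stays hidden. Keeping sequence generation and assignment with assistant researchers protects the list but does not prevent this inference.

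The primary outcome is a behaviour. The Introduction itself names motivation as a driver of adherence, and enrolling staff can form a view of how motivated a patient is. If keener patients were brought forward when AR looked likely to be next, the arms would differ at entry. No measure of motivation is listed under Covariates, so adjustment for the recorded variables could not be relied on to remove the difference.

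**Working it through.** **Inputs.** From the document: 80 allocations, 1:1 (Sample Size), blocked (Study Design). Not in the document and therefore assumed: the block size, one allocation list without strata, and an enroller who sees every earlier allocation in order. The plan gives no predictability figure to reproduce.

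**Predictability.** For a fixed block of 2k patients, k per arm:

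- Share of allocations that are certain (one arm already full, block size known) = 1/(k + 1).
- Share guessed correctly by always naming the under-filled arm, with a coin flip on ties: c = {k + [4^k / C(2k, k) − 1]/2} / (2k). This guess needs only the running imbalance, not the block size.

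Worked for blocks of 4 (k = 2): certain = 1/3, and 80 × 1/3 = 26.7 patients; c = {2 + [16/6 − 1]/2}/4 = 2.833/4 = 0.708.

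| Assumed block | Certain | Of 80 | Guessed correctly |
|---|---|---|---|
| 2 | 50% | 40 | 75% |
| 4 | 33% | 26.7 | 71% |
| 6 | 25% | 20 | 68% |
| 8 | 20% | 16 | 67% |
| 20 | 9% | 7.3 | 62% |

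Chance is 50%. Concealed blocks of random size 4 or 6, simulated, still allow about 69% correct guesses, between the fixed-4 and fixed-6 values.

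**What it could do to the result.** Suppose there is no true effect and the enroller acts on each guess, shifting the entering patient's expected outcome by η standard deviations toward the guessed arm. The expected difference between arms is 2η(2c − 1). With η = 0.25 and blocks of 4: 0.5 × (2 × 0.708 − 1) = 0.21 SD. Rejection rates of a two-sided 5% t test come from 4,000 simulated trials of 80 patients per setting:

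| Block | Rejections, η = 0 | η = 0.1 | η = 0.25 | Simulated difference, η = 0.25 |
|---|---|---|---|---|
| 4 | 4.8% | 6.3% | 15.1% | 0.21 SD |
| 6 | 5.4% | 6.0% | 11.8% | 0.18 SD |
| 8 | 5.2% | 6.3% | 9.9% | 0.17 SD |

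The simulation error near 5% is √(0.05 × 0.95/4000) ≈ 0.3 percentage points. A shift of 0.1 SD therefore does little, while 0.25 SD doubles or triples the false-positive rate. Both values of η are assumptions; nothing in the document suggests that anyone would act this way.

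**The two accounts of entry.** Study Design names case managers as enrollers. Procedure names the principal investigator and a research assistant. Neither says who checks the criteria. The accounts could be consecutive steps (referral and consent, telephone confirmation, then formal entry by a case manager) or two different processes. The text does not settle which.

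**The case against.** The strongest reply is that the document does not show that anyone can predict allocations. It gives no block size, speaks of case managers in the plural, and does not say who runs the AR session. Contact between case managers and the AR arm is inferred from the shared standard care and from the T0 size comparison. Several case managers who each saw only their own patients would predict less well. All of this stands. A reader might infer that case managers can foresee many allocations, but that needs conditions the article does not state.

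Discretion at entry is also limited. Age, Apnea-Hypopnea Index and absence of previous CPAP use are objective, and patients reach the trial after agreeing to CPAP and signing consent. A reader might count the willingness check as a further lever for case managers. Procedure gives that check to the principal investigator, and Study Design says investigators are blinded. What remains is two exclusions and the timing of entry.

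A reader might also infer that the disagreement between Study Design and Procedure itself creates selection bias. It does not. Any bias would come from combining enrolment with knowledge of past allocations under blocking. If Procedure describes the real process, exposure through case managers is smaller.

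Finally, a journal article may leave block size and concealment steps to the full protocol, so their absence is not held against the plan. The reply does not remove the stated combination: case managers enrol, allocation is blocked, a case manager treats controls, and case managers are not listed as blinded.

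**Conclusion.** The point holds as a conditional risk that is cheap to remove. It is not evidence of bias and does not undermine the design. The 20–33% certain and 67–71% guessable allocations are illustrations for fixed blocks of 4 to 8. They hold only if the same case managers enrol and see earlier allocations in order from a single list. Harm further requires that they act on what they infer, and its size depends on how strongly: little at a 0.1 SD shift, about 10–15% false positives at 0.25 SD. The change is still worth making because the outcome is behavioural and the listed covariates could not be relied on to repair such an imbalance. The accounts in Study Design and Procedure need reconciling whichever describes actual practice.

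**What to change.** Amend Study Design so that eligibility and enrolment follow the Procedure route:

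1. The blinded investigator confirms eligibility.
2. A research assistant who neither generates nor holds the sequence logs the enrolment.
3. Case managers take no part in eligibility decisions or in the timing of entry.
4. Each allocation is revealed only after eligibility and consent are logged.

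Recruitment was scheduled to begin in April 2025 and the article appeared on 6 May 2025, so it may already be under way. In that case, apply the change to all remaining patients.

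Varying block sizes, concealed from case managers, can be added if not already used. They are a secondary safeguard of limited benefit, since guesses still succeed about 69% of the time with random blocks of 4 and 6. Separating the roles does most of the work.

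The cost is a wording change and a small change in workflow, using roles the article already names. The article does not show whether the research assistant in Procedure is one of the assistant researchers in Study Design. The amendment must make sure that the person logging enrolment is not the one who holds the sequence.

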### Participants

Patients with OSA will be randomly assigned to either the experimental group or the standard care group.

#### Inclusion Criteria

Our study will enroll adults 20 years or older diagnosed with moderate to severe OSA (Apnea-Hypopnea Index ≥15) confirmed by polysomnography who are CPAP therapy naive at the time of enrollment.

#### Exclusion Criteria

We will exclude those with previous use of positive pressure ventilators, a diagnosis of central sleep apnea, a presence of uncontrolled acute mental illness, or a terminal illness.

#### Sample Size

The sample size was determined based on a power analysis conducted for the CPAP adherence rate. Effect sizes were estimated to be 0.32 based on our previous findings, which indicated that 32.25% of CPAP-related side effects were associated with the CPAP interface [17]. A power of 0.85 was used to detect a significant difference at *P*=.05 (2-sided). Given the highly variable dropout rate for CPAP therapy, we aimed to accommodate a 20% dropout rate, which necessitated recruiting 80 participants, with 40 participants in each group.

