#### Accuracy of Estimated Nasal Size

The AR system’s recommended nasal size compared to the case manager’s estimation shows an agreement rate approaching 95% at T0.

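### The power calculation for CPAP adherence uses a share of side effects (32.25%) as its effect size (0.32), so the stated 85% power has no valid basis for the primary outcome

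*Protocol article*

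**What the plan says.** The Sample Size section of the protocol article names the endpoint it was powered on: "The sample size was determined based on a power analysis conducted for the CPAP adherence rate". It then gives the effect size and its only source: "Effect sizes were estimated to be 0.32 based on our previous findings, which indicated that 32.25% of CPAP-related side effects were associated". The sentence goes on to name the mask interface as what those side effects were linked to. The error rates follow: "A power of 0.85 was used to detect a significant difference" at a two-sided 0.05 level. The total comes from the dropout allowance: "we aimed to accommodate a 20% dropout rate, which necessitated recruiting 80 participants, with 40 participants in each group".

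Two other sections matter. Primary Outcomes calculates adherence as the percentage of days on which CPAP use exceeds 4 hours. Data Analysis plans a mixed-effects model for repeated measures to compare the groups over the visits.

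**The concern.** An effect size for a two-group trial has to describe how far apart the groups are expected to be on the outcome. The 32.25% does not. It splits reported side effects by cause and says what fraction was linked to the interface. It compares no groups, is not measured on adherence, and is not scaled by a standard deviation. The text offers no step from that fraction to a difference in percent of adherent days; 32.25% simply reappears as 0.32.

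What is at stake is how the result will be read. The Introduction states the hypothesis that adherence will be higher with AR, and Study Design presents the trial as an evaluation of effectiveness. A non-significant result would be judged against the advertised 85% power, although the document does not establish that power for any stated adherence effect.

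**Working it through.** **Inputs from the Sample Size section:** effect size 0.32, two-sided alpha 0.05, power 0.85, dropout 20%, 80 participants, 40 per group.

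**Completers implied by the plan:** 80 × (1 − 0.20) = 64, or 32 per group.

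**Inputs the article does not give, so assumed below:** the effect-size metric, the control adherence rate, and the within-patient correlation ρ.

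**1. Can 80 be reproduced?** Read 0.32 as Cohen's f for the between-group effect over m visits. The F test on 1 and N − 2 degrees of freedom has noncentrality λ = f² × N × m / (1 + (m − 1)ρ).

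- m = 3, ρ = 0.55: λ = 0.1024 × 64 × 3 / 2.10 = 9.36, power 0.854. N = 64 is the smallest even total that reaches 0.85, and 64 / 0.80 = 80.
- m = 4, ρ = 0.6: λ = 0.1024 × 64 × 4 / 2.80 = 9.36, power 0.854; again 64, then 80.
- m = 3, ρ = 0.5: 62 needed, 62 / 0.80 = 77.5, so 78.

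So the total is reachable, and T1-T3 alone are enough to reach it.

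**2. Power with 32 per group under other readings of 0.32**

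| Reading of 0.32 | Power | Completers per group for 85% |
|---|---|---|
| Cohen's d, one visit (two-sample t) | 24% | about 177 |
| Cohen's f, so d = 2 × 0.32 = 0.64, one visit | 71% | about 45 |
| Difference in proportions, 30% vs 62% | 74% | 42 |
| Difference in proportions, 40% vs 72% | 74% | 42 |
| Difference in proportions, 50% vs 82% | 78% | 38 |
| Difference in proportions, 60% vs 92% | 87% | 31 |
| Difference in proportions, 5% vs 37% | 90% | 28 |
| Cohen's f, mean of three visits, ρ = 0.5 / 0.7 / 0.8 | 87% / 80% / 77% | 31 / 37 / 39 |

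The same 0.32 therefore gives anything from 24% to 90% power, depending on the reading and the assumed rate or correlation.

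**3. What 64 completers deliver.** At one visit, solving the two-sample t power equation for 85% with 32 per group gives d = 0.761. For the mean of T1-T3, in units of the single-visit SD and assuming equal correlations, multiply by √((1 + 2ρ) / 3):

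- ρ = 0.5: 0.761 × √(2.0/3) = 0.761 × 0.816 = 0.62
- ρ = 0.7: 0.761 × √(2.4/3) = 0.761 × 0.894 = 0.68
- ρ = 0.8: 0.761 × √(2.6/3) = 0.761 × 0.931 = 0.71

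**4. Is there a corrected N?** None can be computed. The article gives no control adherence, expected difference or SD from which to derive an adherence effect.

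**The case against.** The best defence is that the number works. The planned analysis is a repeated-measures model. Under the reading closest to it, f = 0.32 with a plausible correlation returns 64 completers and 80 recruited. A journal article may also leave the metric, SD and correlation to a fuller document. Both points stand: 80 should not be called a calculation error, and the missing metric is not the finding. Neither repairs the input. The article does state where 0.32 came from, and a fuller document could name a metric but could not turn a share of side effects into an adherence difference. The cited earlier study is not available here, so the point rests on the derivation as the protocol words it.

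A reader might infer several stronger things that the documents do not support:

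- **That 80 works only by counting baseline, when CPAP-naive patients have no adherence data.** Three post-baseline visits with ρ = 0.55 give the same total.
- **That the trial can detect only a very large effect.** The 0.76 is for a single visit. The plan is a repeated-measures model and names no primary visit; averaged over T1-T3 the figure is 0.62 to 0.71.
- **That 32.25% caps the benefit, because AR could at most rescue that share of non-adherent patients.** The protocol states no such model, and it expects AR to act through motivation, skills and troubleshooting as well.
- **That the "agreement rate approaching 95% at T0" for mask size leaves AR little to change.** Sizing is one component; the system also checks the wearing procedure. The figure has no bearing on the power calculation.

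**Conclusion.** The point holds as a fault in the justification of an input. The effect size of 0.32 is a proportion of side effects relabelled as an adherence effect, so the 85% power is unsupported for the primary outcome. This conclusion needs no assumption beyond the protocol's own description of the 32.25%.

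The size of the problem does depend on assumptions. With 64 completers, power for 0.32 is 24% if it is d. It is 71% if it is f at one visit, and 74-78% if it is a difference in proportions with control adherence of 30-50%. It is about 77-87% if it is f averaged over three visits with correlation 0.8 down to 0.5. The last range includes the stated 85%, so the power is best called undocumented rather than shown to be wrong.

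**What to change.** Delete the sentence deriving 0.32 from the 32.25%. Keep 80 participants and replace the derivation with a statement of what they deliver under the planned analysis, for example:

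*With 64 completers (80 less 20%) and two-sided alpha 0.05, the trial has 85% power to detect a standardised difference in percent of adherent nights, averaged over T1-T3, of about 0.62, 0.68 or 0.71 if the within-patient correlation is 0.5, 0.7 or 0.8 (assumed), and of about 0.76 at any single visit.*

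Add the matching difference in percentage points, using an SD taken from adherence data. State that a non-significant result will be interpreted through the estimate and its 95% confidence interval, and not as evidence of no effect.

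The cost is a rewritten paragraph. The detectable effect will look less favourable than the printed 0.32. The number of patients, the visits and the analysis do not change.
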